### Sample size

Our estimate is based on the effect observed by Dahinten (2014) on the overall score for structural empowerment. Given the hierarchical structure of the data in the present study, (“professional” level nested in the ‘“functional unit” level, in turn nested in the “department” level) an inflation factor needs to be applied to the standard calculation of sample size [78]. The calculation of the inflation factor is based on the following hypotheses:
an intra-class Correlation Coefficient (ICC) equal to 0.001 (within-SC correlation) We did not find any estimation in the literature of an ICC corresponding to our main judgement criterion and our study population. However ICC values are classically around 0.001 to 0.1 [79]an alpha risk of 5%a statistical power of 80%a difference of 0.12 points between global structural empowerment scores for professionals in the intervention group between T1 and T2 [42]a standard deviation of the global structural empowerment score of 0.56 points [42]

With these hypotheses, the number of professionals to include per group is 519. In all, 1038 professionals should be included. This expected number is close to the overall numbers of professionals in the two SCs. Given the considerable risk of loss to follow-up, the choice was to aim for an exhaustive coverage of the two SC, i.e. 600 to 700 individuals per group. We also rely on the compulsory nature of the check-up to reach this objective.

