### Statistical analysis

At the outset, the psychometric quality of the concepts measured in the questionnaires will be tested by exploratory and confirmatory factor analysis as well as an exploratory structural equation modelling. These analyses will enable the confirmation of the internal validity of the concepts postulated in the measurement scales and will, if needed, enable the adjustment or rejection of invalid in our sample. The analyses will be conducted under Mplus8 for Windows.

At the individual level, mixed linear models will used to assess the effects of the intervention on each outcome, while taking into account the hierarchical nature of the data, and possible variations in the implementation of the intervention protocol from one department or unit to another. The score of an outcome at T2 is thus explained by the fixed SC effect (intervention versus control) and by the random effect of the department or unit. A statistical adjustment will be made on the outcome score at T0 and on age, gender, profession, working time and size of the team, in line with the literature [36, 80]. The ICC will be estimated to have a precise idea of the effect of the department or unit.

Given the results obtained by Dahinten (2014), which showed a moderating effect of the level of implication at T0 on the impact of the intervention on implication at T1, a second model will be run each time including an interaction terms between the SC group and baseline measures of the outcome variable. These analyses should enable the identification of conditions that favour or undermine the interventions’ effect and implementation.

For the psychometric scales more particularly, the analyses will be performed on both the overall scores and the sub-dimension scores so as to refine the analysis of the effects as far as possible.

At the department and unit level, the score for each outcome will be calculated at T0 and T2 in each group. Mixed-effects linear models will be used to test the effects of the intervention over time, and between departments or units. These analyses will enable the study of variations in the effects of the intervention across the “intervention SC” departments or units.

The alpha risk retained for the statistical analysis is 5%. If the proportion of missing data exceeds 30%, multiple imputation will be considered.

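### The SC-by-baseline interaction is added to a model whose only stated random term is a department or unit effect, so its 5% test rejects too often if the T0-to-T2 slope differs between those clusters

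*Protocol article*

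**What the plan says.** The Statistical analysis section of the Protocol article describes an individual-level mixed linear model. The T2 score is "explained by the fixed SC effect (intervention versus control) and by the random effect of the department or unit", with adjustment for the T0 score and several personal and team characteristics. An ICC is to be estimated for the department or unit effect. The section presents this structure as its way of dealing with the hierarchy and with "possible variations in the implementation of the intervention protocol from one department or unit to another".

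On moderation it then says that "a second model will be run each time including an interaction terms between the SC group and baseline measures of the outcome variable". The stated purpose is to find conditions that help or hinder the intervention. Psychometric scales are analysed on both total and sub-dimension scores. On the error rate the section says "The alpha risk retained for the statistical analysis is 5" per cent.

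Sub-centers recruitment gives five to six departments and 20 to 25 care units per SC. One SC receives the intervention and one is the control.

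**The concern.** SC membership does not vary within a department or unit, while the T0 score varies from person to person. Their product is a cross-level interaction. A random intercept lets cluster means differ but holds the T0 slope equal in every cluster of the same SC. If the slopes in fact differ, the between-cluster variation in slope is missing from the standard error, and the interaction is credited with the precision of over a thousand individuals instead of that of some 40 to 50 units or 10 to 12 departments.

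Ordinary differences between units could then be reported as evidence that the programme works better or worse for staff who start low or high. The test is repeated for each outcome and sub-dimension, so there would be many chances for this to happen.

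**Working it through.** **1. The plan's own figure.** The article states no error rate or power for the interaction, so the figure to reproduce is the sample size. The inputs are "an alpha risk of 5" per cent (taken as two-sided), "a statistical power of 80" per cent, "a difference of 0.12 points between global structural empowerment scores" and "a standard deviation of the global structural empowerment score of 0.56 points", with an ICC of 0.001.
- Unadjusted: 2 × (1.960 + 0.842)² × 0.56² / 0.12² = 341.9, so 342 per group.
- Design effect with the whole SC as the cluster: 1 + (519 − 1) × 0.001 = 1.518.
- 342 × 1.518 = 519.2, which matches the stated 519.

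Nothing below changes that number.

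**2. Inputs for the interaction test.**
- From the article: 20-25 units or 5-6 departments per SC, and 519 professionals per group, with 600-700 targeted.
- Assumed, because the article does not give them: a mean standardised T0-to-T2 slope of 0.5, an intercept ICC of 0.02, and a between-cluster SD of the slope, s, from 0 to 0.15.

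**3. Approximation.** With m people per cluster and residual variance 1 − 0.5² = 0.75, the random-intercept standard error is too small by the factor √(1 + m·s²/0.75). The true rejection rate of a nominal 5% test is 2 × [1 − Φ(1.96/factor)].
- Units, m = 26, s = 0.10: factor √(1 + 0.26/0.75) = 1.160; 1.96/1.160 = 1.689; rate 9.1%.
- Departments, m = 104, s = 0.10: factor √(1 + 1.04/0.75) = 1.545; 1.96/1.545 = 1.269; rate 20%.

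If slopes vary in one SC only, the excess variance is halved:
- Units, m = 26: factor √(1 + 0.26/1.50) = 1.083; rate 7.0%.
- Departments, m = 104: factor √(1 + 1.04/1.50) = 1.301; rate 13%.

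**4. Simulation.** There were 1,500 runs per cell with no true interaction, using a REML random-intercept fit and a Wald test at 1.96. The both-SC columns cover 20, 23 or 25 units, or 5 or 6 departments, per SC, with 519 or 650 people per SC. The one-SC columns use 44 units of 28 and 12 departments of 104.

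| Assumed slope SD | Units, both SCs | Departments, both SCs | Units, intervention SC only | Departments, intervention SC only |
|---|---|---|---|---|
| 0 | about 5% | about 5% | – | – |
| 0.05 | 6-8% | 8-11% | 6% | 7% |
| 0.10 | 8-10% | 19-24% | 7% | 12% |
| 0.15 | 12-16% | 29-37% | 9% | 21% |

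**5. Comparator.** In the both-SC simulations, a t-test comparing cluster-specific T0 slopes between SCs rejected in about 4-6% of runs in every scenario. Those scenarios contain no slope difference belonging to an SC as a whole.

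**6. What the comparator cannot do.** With no true moderation, a cluster slope SD of 0.10 and an SC-level slope SD of 0.05 or 0.10 (both assumed), the same t-test rejected in 19% or 43% of runs with units, and in 14% or 32% with departments.

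**The case against.** **The text is condensed.** The single random effect is stated for the first model. The second is covered in one clause, and a fuller plan could add a random slope. That possibility stands. Even so, the article names one random term, summarises it by an ICC and describes the second model only as adding an interaction. Followed as written, the problem is there.

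**Varying delivery need not mean varying slopes.** Uneven implementation would first shift unit means, which the intercept absorbs. It can also occur only in the intervention SC, because the control SC runs as usual. This stands in large part, and it is why the lower one-SC rates are reported beside the others.

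**Stronger readings.** A reader might infer that the test rejects some fixed multiple too often, for example two to six times. The documents do not support that, because they give no slope SD. At SD 0.05 between units the rate is only about 6-8%, and at SD 0 there is no inflation. A reader might also infer that the 20-25 units per SC are the true replication and that a cluster-level test fully restores the 5% level. That does not hold either. Allocation is one SC against one SC, and step 6 shows the cluster-level test failing once the SCs themselves differ in slope.

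**Conclusion.** The point holds conditionally. As described, the interaction test is anti-conservative whenever T0 slopes differ between units or departments, and the article's own expectation of uneven implementation makes this possible without establishing it. The direction is certain once slopes vary. The size is not, because it rests on the assumed slope SDs, on the mean slope of 0.5, on whether the random effect is for units or departments, and on whether slopes vary in one SC or both. Departments are the more exposed choice.

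This is a secondary moderation analysis. The amendment is worth making because the remedy is a better method at little cost, but it removes only part of the error: the confounding of SC with intervention remains.

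**What to change.** In the second model:
- add a random slope for the T0 score at the same department or unit level as the random intercept;
- centre T0, so that the SC term is the effect at average baseline;
- test the interaction with cluster-level degrees of freedom;
- if the slope variance cannot be estimated, which is a real prospect with 10-12 departments, estimate the T0 slope in each cluster and compare the two SCs with a t-test.

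State also that, with one SC per arm, neither test can tell a slope difference particular to one SC from moderation by the intervention, and that interaction results will be reported as exploratory.

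The cost is analysis-plan wording, wider intervals for the interaction and occasional non-convergence. No change to data collection or sample size is needed.

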Since the early days, in the 1970s and 1980s, empowerment has been seen as a multi-level concept [6, 10, 11]. On the individual level, Thomas & Velthouse (1990), [15, 16, 21] conceptualised psychological empowerment as the creation of a system of cognitions (beliefs and attitudes) based on experience (and its subjective interpretation), which can be likened to systems of expectations of an individual in relation to his or her abilities, level of implication and performances, and this in turn is predictive of attitudes and behaviours such as commitment to the job and actual performance. This involves the belief entertained by an individual that he/she 1) has an impact on the professional environment, 2) that he/she possesses the required professional skills, 3) that his/her professional actions are the result of his or her own will-power, and 4) that his/her work has meaning.

On the environmental level, structural empowerment [14, 22] for its part relates to the social, physical and organisational components of the environment that favour, predict or mediate the influence, control or power of social actors. Here the issues are access to 1) opportunities for professional development, 2) relevant information on the enterprise and its strategies, 3) adequate support to enable and contribute to personal development, and 4) the possibility of exerting an influence to obtain more resources (funds, equipment, human resources).

The effects of psychological [23] and structural empowerment in care facilities have been widely studied in the literature. Whatever the level of implementation, favourable effects are observed on job satisfaction [24–27], caregiver health [25, 28–31], the intention to stay in the facility [30, 32, 33], commitment [24, 34, 35], innovation [16, 21, 36], management efficiency [16], implication in unplanned pro-organisational behaviours [31, 37], care quality [4, 38, 39], and performance generally [4, 37]. The psychological and structural levels of empowerment are thus relevant intervention targets, liable to achieve an overall improvement in the performances of care facilities.

To our knowledge, there are six controlled interventional studies in care environments that have targeted empowerment among first-line professionals.

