### Sub-centers recruitment

The targeted CHU comprises 12 SCs with five to six departments each, each in turn grouping a number of care units for a total of 20 to 25 per SC. The size of the SCs varies from 800 to more than 1000 salaried staff. The hierarchical structure is presented in Fig. 2.

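### Tying multiple imputation to a 30% missing-data threshold, with a T2-only model, leaves the T2 contrast open to bias below 30% if loss depends on post-baseline empowerment and differs between the two sub-centres

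*Protocol article*

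**What the plan says.** **Missing-data rule.** The Statistical analysis section of the protocol article gives a single measure: "If the proportion of missing data exceeds 30%, multiple imputation will be considered". It names no method at or below 30%. Above 30% it commits only to considering imputation.

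**Model.** The same section specifies the individual-level analysis: "The score of an outcome at T2 is thus explained by the fixed SC effect (intervention versus control) and by the random effect of the" (quote cut here; the grouping level is unit or department). The covariates are given next: "A statistical adjustment will be made on the outcome score at T0 and on age, gender, profession, working time and size of the team". T1 does not appear in this model, although the Study design section schedules an assessment at the end of the intervention and the Objectives ask for effects at both one and two years. The department- and unit-level analysis also uses T0 and T2 only.

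**Expected loss.** The Sample size section requires 519 professionals per group and then says, of the number in each group: "Given the considerable risk of loss to follow-up, the choice was to aim for an exhaustive coverage of the two SC, i.e. 600 to 700". It relies on the check-up being compulsory to reach that number.

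**Link between empowerment and staying.** The Background lists "the intention to stay in the facility" among the outcomes that empowerment improves.

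**SC size.** The Sub-centers recruitment section says: "The size of the SCs varies from 800 to more than 1000 salaried staff".

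**The concern.** The random effect in the model is for department or unit, not for repeated measurements on the same person. Each person contributes one outcome value. A participant measured at T0 and T1 but absent at T2 therefore contributes nothing, and the T1 score, usually the best predictor of the missing value, is not used.

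Whether that biases the comparison depends on why people are missing, not on whether the proportion passes 30%. The intervention is meant to raise empowerment in one SC only, and the article itself connects empowerment with staying. It is therefore plausible that leaving is related to empowerment after baseline, and that the relation is not the same in both SCs. Adjusting for T0 does not remove selection of that kind. At stake is the two-year contrast on structural empowerment, the first listed objective, and on every other outcome analysed the same way.

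**Working it through.** **1. The plan's sample size.** Inputs from the Sample size section: difference 0.12, SD 0.56, ICC 0.001, "an alpha risk of 5"%, "a statistical power of 80"%. Sidedness is not stated; two-sided is assumed because it reproduces the figure.

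- Without clustering: 2 × [0.56 × (1.960 + 0.842) / 0.12]² = 341.9, so 342 per group.
- With design effect 1 + (n − 1) × 0.001, where n is the whole group: n = 342 × 0.999 / (1 − 0.342) = 519.2. This reproduces 519. It contains no allowance for loss and no gain from T0 adjustment.

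**2. Loss that 600 to 700 can absorb.**

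- 1 − 519/600 = 13.5%; 1 − 519/700 = 25.9%.
- At 30% loss: 600 × 0.70 = 420; 700 × 0.70 = 490.

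**3. Power at 420 and 490.** Effective size is n / [1 + (n − 1) × 0.001], and power is Φ(0.12 / [0.56 × √(2/n_eff)] − 1.96).

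- Unadjusted: 420/1.419 = 296, power 74.1%; 490/1.489 = 329, power 78.5%.
- With T0 adjustment and an assumed T0–T2 correlation of 0.5, the SD is multiplied by √(1 − 0.25): power about 85% and 89%. If T0 adjustment removes none of the between-SC variance, 82% and 85%.

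**4. Bias of the T2 model, by simulation.** The documents give no loss mechanism and no correlations between visits, so these are assumptions. The true effect is 0.12 throughout. *Using T1* means imputing T2 from T0 and T1.

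Setting A: SD 0.56, correlations 0.5 to 0.6, 29% lost, log-odds of loss rising as T1 falls.

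| Slope per SD of T1 (control / intervention) | T2 model adjusted for T0 | Using T1 |
|---|---|---|
| 1 / 0 | 0.075 to 0.080 | about 0.12 |
| 1 / 0.5 | 0.099 to 0.102 | about 0.12 |
| 1 / 1 | 0.120 to 0.121 | about 0.12 |

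The ranges cover repeated runs with slightly different correlations. The shortfall is (0.12 − 0.075)/0.12 = 37.5% of the effect in the first row and roughly (0.12 − 0.10)/0.12 = 17% in the second. By symmetry, a steeper slope in the intervention SC would push the estimate upwards.

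Setting B: 650 per group, about 30% lost, T0–T1 correlation 0.5, T2 generated mainly from T1.

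| Loss depends on | T2 model adjusted for T0 | Using T1 |
|---|---|---|
| T0 only (both SCs, or control only) | 0.119 to 0.120 | 0.119 to 0.120 |
| T1, both SCs | 0.112 | 0.119 |
| T1, control only | 0.049 | 0.120 |
| T2 itself, both SCs | 0.102 | 0.106 |
| T2 itself, control only | about 0.00 | 0.040 |

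The bias is material when dependence on T1 differs by SC, and using T1 removes it. When loss depends on the unseen T2 score, using T1 helps only in part.

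**The case against.** **This is a condensed article, and it never says complete-case.** True: exclusion of people without T2 is inferred from the model. The article also does not say whether the 30% refers to lost participants or to missing values per variable. But the threshold is a written rule, so the point is about what is stated, not about detail left to a fuller document.

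**The bias needs a particular mechanism.** This stands. The Background speaks of intention to stay, not of observed leaving, and gives no rate. No passage shows that the dependence differs between SCs. With equal dependence, or dependence on T0 alone, the planned model is close to unbiased.

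**The check-up is mandatory, with a letter and up to two telephone reminders.** This should limit loss, but research participation is voluntary, people who leave are no longer called, and the article still expects considerable loss.

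**Stronger readings that the documents do not support.**

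- A reader might infer that the 30% rule takes the sample below 519, or that the plan accepts 30% loss. Loss itself reduces the number, no method of analysis restores unobserved T2 scores, and 30% is only the point at which imputation would be considered.
- A reader might take 74% to 78% as the trial's power at 30% loss. That ignores the planned T0 adjustment, which could keep power above 80%.
- A reader might conclude that 600 to 700 is partial coverage and that non-participation is already built in. The 800 to more than 1000 counts all salaried staff, whereas the study enrols consenting professionals in healthcare departments; the eligible numbers in the two selected SCs are not given. If 800 to 1000 were enrolled, 30% loss would leave 560 to 700, above 519.

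**Conclusion.** The concern holds in a conditional form. A percentage threshold is a poor basis for choosing a missing-data method, and the T2-only model discards T1 information that could protect the estimate. If loss depends on T1 and differs between SCs, the planned contrast can fall to about 0.075 to 0.10 against a true 0.12 at 29% loss (correlations 0.5 to 0.6). Under the stronger T1–T2 link of setting B it falls to 0.049. These sizes rest on assumed mechanisms that the article makes plausible but does not quantify; they are not forecasts.

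The sample-size matter is separate and smaller. The loss allowance implied by 600 to 700 is 13.5% to 25.9% and is not stated, and the description of that target as exhaustive does not sit easily with the SC sizes given elsewhere. Neither shows that the trial is underpowered.

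**What to change.** 1. **Delete the 30% threshold.** Suggested wording: *Whatever the proportion of missing data, the T2 effect will be estimated from a likelihood-based repeated-measures model of the T0, T1 and T2 scores, with within-person correlation and random effects for unit and department.* An acceptable alternative is multiple imputation within arm that includes T1 and respects unit and department.
2. **Add one delta-adjusted sensitivity analysis.** Shift the imputed T2 scores of people lost to follow-up over a stated range, allowing different shifts by SC, because T1-based methods do not fully correct loss that depends on T2.
3. **State the loss allowance.** Say that 600 to 700 per group keeps the 519 of the unadjusted calculation up to 13.5% to 25.9% loss, and that T0 adjustment may offset the loss of power beyond that.
4. **Reconcile the coverage figures.** Give the number of eligible professionals in each selected SC, so that the 600 to 700 target can be read against the 800 to more than 1000 staff.

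**Cost:** revised wording and some extra programming; no new data. The main analysis will assume data missing at random given T0 and T1, which should be stated, and it will not recover the precision lost with unobserved T2 scores.

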### Data access

The data is collected using an online file completed by the participant or the research staff on computer or tablet. The website and the database are run on the secure Data Management in the CHU. The data collected in the course of the study will be kept in a computerised file in compliance with present French law (*Informatique et libertés,* January 6th 1978, modified in 2004) [81].

The health data of the participants is transferred only to the body to which the researcher in charge of the study is attached, or to any person authorised by him in compliance with confidentiality requirements. The body to which the investigator is attached can request direct access to the medical files to check on procedures and/or the research data, without breaching confidentiality and within the limits of the law. Within the present study, an inspection or audit can be performed. The promoter should be able to grant access to the data for inspectors or auditors. The investigator is to keep all the information relating to the study for at least 15 years after the end of the study.

